### Adjusting variables

The randomisation is stratified according to the nationality of the participating centres and, within each stratum, the patient allocation is based on probabilistic minimisation (80:20) using the following factors:Intention to perform thrombolysis (yes compared to no).Method of cooling (surface compared to endovascular).Sex (male compared to female).Stroke severity (National Institutes of Health Stroke Score (NIHSS)) 6–12 compared to 13 or higher).Age (≤ 65 years compared to > 65 years).Visibility of a relevant ischaemic lesion on the first brain imaging (yes compared to no).Time since symptom onset (≤ 4 hours compared to 4–6 hours).

The primary analyses will be adjusted by the protocol-specified stratification variable country and the seven minimisation factors.

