**Methods/design:**

The EuroHYP-1 trial is a multinational, randomised, superiority phase III clinical trial with masked outcome assessment testing the benefits and harms of therapeutic cooling in awake adult patients with acute ischaemic stroke. The outcomes dealt with here include the *primary outcome* the Rankin score (mRS) at day 91 +/-14 days after randomisation. The *secondary and exploratory outcomes* at day 91 +/-14 days unless otherwise stated encompassing: (1) death or dependency, defined as mRS score > 2; (2) death; (3) National Institutes of Health Stroke Score; (4) brain infarct size at 48 +/-24 hours; (5) EQ-5D-5 L score, and (6) WHODAS 2.0 score. Other outcomes are: the *primary safety outcome* serious adverse events; and the incremental cost-effectiveness, and cost utility ratios. The *analysis sets* include (1) the intention-to-treat population, and (2) the per protocol population. The sample size is estimated to 800 patients (5% type 1 and 20% type 2 errors). All analyses are adjusted for the protocol-specified stratification variables (nationality of centre), and the minimisation variables. In the analysis, we use ordinal regression (the primary outcome), logistic regression (binary outcomes), general linear model (continuous outcomes), and the Poisson or negative binomial model (rate outcomes).

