## Methods

### Objective of the EuroHYP-1 trial

The primary aim of the EuroHYP-1 trial is to determine whether systemic cooling to a target temperature of 34–35 °C, started within 6 hours of onset of stroke and maintained for up to 12 hours thereafter, improves outcomes in patients with acute ischaemic stroke. Inclusion and exclusion criteria are described in the design article in Tables 1 and 2 [1].

**Table 1 Tab1:** Baseline characteristics of the participants in the EuroHYP-1 trial

Baseline characteristics	Intention-to-treat population		Per protocol population	
	Intervention group	Control group	Intervention group	Control group
Centre				
- name of centre 1, N (%)				
- name of centre 2, N (%)				
- name of centre 3, N (%)				
- etc				
Intention to perform thrombolysis, N (%)				
Surface cooling, N (%)				
Males, N (%)				
Stroke severity (NIHSS), mean (SD), N				
Age ≤ 65 years, N (%)				
Age, mean (SD), N				
Visible ischaemic lesion on brain imaging, N (%)				
Time since symptom onset, N ≤ 4 hours (%)				

*NIHSS* National Institutes of Health Stroke Score, *SD* standard deviation

**Table 2 Tab2:** Power (based on an α = 0.05) of the secondary outcomes and serious adverse events provided inclusion of 800 patients into the EuroHYP-1 trial

Outcome	Proportion or mean value in control group	Standard deviation in the control group for continuous outcome	Minimal relevant intervention effect - absolute risk reduction relative to control group	Power
Score of NIHSS at 91 +/-14 days (sample size = 800)	8 points^a^	5 points^a^	2 points^a^	1.00
Serious adverse events at 91 +/-14 days (sample size = 800)	20%	NR	10%	0.98
Death or dependency, defined as modified Rankin score > 2 at 91 +/-14 days (sample size = 800)	63%	NR	7.25%	0.55
Brain infarct size at 48 +/-24 hours (sample size = 800)	10 ml^a^	15 ml^a^	2 ml^a^	0.47
EQ-5D-5 L score at 91 +/-14 days (sample size = 800)	0.50 points	0.40 points	0.05 points	0.42
Death at 91 +/-14 days (sample size = 800)	17%	NR	3.84%	0.33

*NIHSS* National Institutes of Health Stroke Score, *EQ-5D-5 L* EuroQoL quality-of-life scale, *NR* not relevant

^a^Assumed values

The null hypothesis is that there is no difference in death and disability as defined by a score on the modified Rankin Score (mRS) scale measured at 91 +/- 14 days after randomisation of the patient.

For an overview of patient schedule and data collection see Fig. 1.

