
### The sample size

Originally, we planned to demonstrate or reject an absolute difference of 7% between the intervention groups (equivalent to an odds ratio (OR) of 0.74) and allowing for 3% loss to follow up in a sample size of 1500 randomised patients with a type 1 error risk of 5% and a type 2 error risk of 10% (EuroHYP-1, EudraCT number 2012-002944-25, version 2, 20 December 2012). Due to exceptionally slow enrolment, we realised that this target was no longer realistic. Accordingly, in 2014, the sample size was downgraded to 800 patients based on considerations explained in version 4 of the protocol (EuroHYP-1, EudraCT number 2012-002944-25, European Database on Medical Devices (EUDAMED) number CIV-12-09-008821, planned trial period July 2013 to March 2017 (45 months), version 4, date 29 June 2015). Currently, the project has been prolonged until 31 July 2018.

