### Statistical analyses

#### Analytical principles

Analyses will be conducted according to the intention-to-treat principle [2] if not otherwise stated.

All primary tests of significance will be two-sided with alpha = 5%. Analyses will be conducted blinded with the two intervention groups coded as, e.g. 0 and 1. Two conclusions will be drawn, one assuming 0 is the intervention group and 1 is the control, and one assuming the opposite. After two abstracts with two conclusions have been written and both accepted by the Steering Group, the code will be broken.

The primary analyses of primary, secondary, and exploratory outcomes will be those of the intention-to-treat population adjusted for the protocol-specified stratification variable and the minimisation variables, and if necessary using data sets generated using multiple imputation.

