#### Missing values of the primary outcome

By definition, none of the adjusting variables will have missing values (otherwise the stratification and minimisation could not have been conducted). So only the outcome value may be missing. Furthermore, we assume there are no useable auxiliary variable, i.e. no other variable that has a moderate to high correlation with the outcome (|r| > 0.40) and yet is not intended to be a predictor in the regression model. In this situation, the problem is easily solved. If we are willing to assume that the data are missing at random, the maximum likelihood analysis reduces to a complete case analysis [3, 4]. Consequently, we simply delete participants that are missing on the outcome and estimate the regression with the remaining participants. However, if useable auxiliary variables have been identified, a multiple monotone imputation will be conducted, which will include the primary outcome and the covariates of the analytical model plus the auxiliary variables. As a sensitivity analysis to assess the potential impact of outcome values missing not at random (MNAR), we will conduct a worst/best case scenario imputation, i.e. a single value imputation of the missing values. The imputations use a minimum value or a maximum value (0 respectively 5 of the modified Rankin scale in that we assume that a patient who died will not have the mRS value missing). Missing values are imputed by the minimum value in one intervention group, and in the other intervention group by the maximum value and vice versa. Once the randomisation code is broken the results of the two comparisons may be interpreted.

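### Age and baseline NIHSS are specified for adjustment only in two-level minimisation form although actual values are collected, which gives up a modest amount of power in the primary ordinal model

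*SAP article*

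**What the plan says.** The section Adjusting variables lists seven minimisation factors within country. Stroke severity enters as NIHSS "6–12 compared to 13 or higher" and age as "Age (≤ 65 years compared to > 65 years". The section then says: "The primary analyses will be adjusted by the protocol-specified stratification variable country and the seven minimisation factors". Analytical principles applies the same adjustment to the primary, secondary and exploratory outcomes in the intention-to-treat population.

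Missing values of the primary outcome treats the model covariates as the variables used in allocation: "By definition, none of the adjusting variables will have missing values (otherwise the stratification and minimisation could not have been conducted". No section gives a continuous form for either variable.

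Table 1 has a row "Stroke severity (NIHSS), mean (SD), N" and a matching mean and SD row for age, next to the row for age at or below 65. The actual values are therefore collected.

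On size, the abstract says: "The sample size is estimated to 800 patients (5% type 1 and 20% type 2 errors". The section The sample size says that "the sample size was downgraded to 800 patients based on considerations explained in version 4 of the protocol". The table of amendments gives improved power as the reason for adding nationality to the model.

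**The concern.** Cut points are needed to run a minimisation, but the model does not have to reuse them. A patient with NIHSS 13 and one with NIHSS 25 get the same covariate value, as do patients aged 66 and 90. If age and baseline severity predict the mRS within those bands, the two-level terms leave that variation unexplained and the treatment test loses power.

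The loss matters more here because the target fell from 1500 to 800, and because under the fixed-sequence procedure a non-significant primary outcome ends confirmatory testing. Having amended the plan to adjust for nationality for the sake of power, the authors left a further gain from data already collected unused.

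**Working it through.** **Inputs from the SAP article.** N = 800; two-sided alpha 0.05; common odds ratio (OR) 0.74; 63% of controls with mRS > 2; 17% control mortality; covariate cut points as above.

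**Assumed inputs, not in the article.** 1:1 allocation; the full control mRS distribution; the distributions of age and NIHSS; how strongly each predicts the mRS; linear effects on the log-odds.

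**Step 1: the plan's own figures.** For a proportional-odds comparison with 1:1 allocation, V = (N/12)(1 − Σp̄³), where p̄ are the mean category proportions of the two arms, and power = Φ(|ln OR|·√V − 1.96). Take an assumed control distribution for mRS 0 to 6 of 8, 15, 14, 16, 20, 10 and 17%, which has 16 + 20 + 10 + 17 = 63% above 2. At OR 0.74, Σp̄³ = 0.0239.

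- Original design, 90% power: N = 12(1.96 + 1.2816)² / (0.3011² × 0.9761) = 1425, and 1425/0.97 = 1469 after 3% loss. Two other assumed distributions extend the range to 1466–1477. This agrees with 1500 to within 3%.
- Current size: V = (800/12) × 0.9761 = 65.1; 0.3011 × √65.1 − 1.96 = 0.47; unadjusted power 0.68. An 80% power at 800 would need an OR of about 0.71. The inputs behind 800 are in protocol version 4, which is not shown, so this is not counted as an error.

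**Step 2: simulation with age and NIHSS only.** There were 2,000 trials of 800 patients per setting. Age was about N(70, 12), with 66% over 65. NIHSS was 6 or more, with mean 11.8, SD 4.7 and 35% at 13 or higher. Country and the other five factors were omitted. Three models were fitted to the same data. Relative efficiency is (z continuous / z two-level)², with z the mean estimate over the mean standard error. Extra patients are 800 × (relative efficiency − 1). The marginal OR was set at 0.74.

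| OR per 10 years / per NIHSS point | Unadjusted | Two-level | Continuous | Gain (points) | Relative efficiency | Extra patients |
|---|---|---|---|---|---|---|
| 1.22 / 1.08 | 0.681 | 0.699 | 0.712 | 1.3 | 1.022 | 18 |
| 1.35 / 1.13 | 0.670 | 0.720 | 0.746 | 2.6 | 1.058 | 46 |
| 1.49 / 1.17 | 0.680 | 0.746 | 0.777 | 3.1 | 1.089 | 71 |
| 1.65 / 1.22 | 0.662 | 0.756 | 0.810 | 5.4 | 1.149 | 119 |

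Monte Carlo error is about √(0.7 × 0.3/2000) = 0.010 per power figure, and less for the paired differences. With the conditional OR fixed at 0.74 instead, the pairs are 0.682 v 0.692, 0.658 v 0.679, 0.618 v 0.648 and 0.609 v 0.670, a gain of 1 to 6 points.

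**Step 3: a second simulation with other assumptions.** There were 3,000 trials per setting, 12 countries, 33.7% with NIHSS 13 or higher, 63% over 65, and a latent R² for NIHSS plus age of 0.14, 0.23 and 0.30. Two-level power was 0.74, 0.76 and 0.78; continuous power was 0.76, 0.80 and 0.84. Relative efficiency, ((z of continuous power + 1.96)/(z of two-level power + 1.96))², was 1.04 to 1.16; the rounded powers reproduce both ends to within 0.01. Type I error stayed near 5%.

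**Where the gain comes from.** In the strongest setting of Step 2 the mean log OR moves from −0.333 (two-level) to −0.360 (continuous), while the standard error hardly changes (0.1257 v 0.1267). As usual in an ordinal logistic model, better covariates move the conditional estimate away from the null rather than shrink its standard error.

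**The case against.** Adjusting for the variables used in allocation is pre-specified, coherent and valid. Nothing in the article is misstated on this point, and chance imbalance within the bands is random variation that the confidence interval already covers. This stands: the point is about efficiency, not bias.

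The article never says in so many words that the two factors are coded as dichotomies in the model. That is an inference, but the dichotomies are the only form it defines, and the missing-data section ties the covariates to the allocation variables.

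The size rests on inputs the article does not give, and the Step 2 simulation generated linear effects and fitted linear terms, which favours continuous covariates. This stands and is why a range is given.

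A reader might infer that dichotomising is why 80% power is missed at OR 0.74. The documents do not support that. Continuous terms also miss 80% in three of the four settings in the table, unadjusted power is already about 0.68, and the basis for 800 lies in a protocol version not shown.

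A reader might also infer a gain for every secondary outcome. None was simulated, and Table 2 already gives power 1.00 for NIHSS and 0.98 for serious adverse events, where any gain would be negligible.

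Finally, if the proportional-odds assumption is rejected, the primary result is a van Elteren test stratified by nationality alone, and neither covariate enters. Read literally, the acceptance rule asks that all category differences share one sign. Proportions sum to one in each arm, so those differences sum to zero and the rule could not be met. In that branch the proposed change does nothing for the primary result.

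**Conclusion.** The point holds as an avoidable inefficiency in a valid analysis. In the primary ordinal model at 800 patients and a marginal common OR of 0.74, two-level age and NIHSS cost about 1 to 6 power points against continuous terms, equal to roughly 2% to 16% more patients. The direction was the same in every setting of two simulations with different assumptions. The size depends on prognostic strength, which the article does not state, and on roughly linear effects. It applies only when the adjusted ordinal model supplies the primary result. For secondary outcomes the same principle applies, but no figure is offered.

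**What to change.** Before unblinding, add one sentence to Adjusting variables: age and baseline NIHSS enter the primary ordinal model and the regression models for the secondary outcomes as continuous covariates (linear, or one pre-specified spline) in place of their two-level versions. Country and the other five factors stay as randomised, and the all-dichotomised model is reported as a sensitivity analysis.

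The costs are small but not nil. The functional form must be fixed in advance. Completeness of the actual age and NIHSS values must be checked, because the argument that covariates cannot be missing by definition covers only the allocation categories. The reported OR becomes conditional on finer covariates, which the text should say. No new data are needed.

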### Flow of patients and baseline characteristics

The flow of patients will be reported according to the CONSORT guidelines (Fig. 2). Patients’ baseline characteristics will be reported in a table (Table 1) for the intention-to-treat population and for the per protocol population.

**Fig. 2 Fig2:**
[figure not shown]
Flow of participants in the EuroHYP-1 trial

### Definition of the efficacy and safety outcomes

Outcomes in the original statistical analysis plan (SAP) included in the EuroHYP-1 protocol are defined as primary, secondary, and exploratory. In the present SAP, we deal only with the primary and secondary outcomes as well as one safety outcome and one health-economic outcome. For information on the exploratory outcomes mentioned and defined in the EuroHYP-1 trial protocol and the analyses of these outcomes the reader is therefore referred to the protocol [1].

#### The primary outcome

The primary outcome is degree of disability post stroke as measured by the seven-level modified Rankin Scale measured in the period 91 ± 14 days after the patient’s randomisation.

#### The secondary outcomes originally selected

The order of secondary outcomes as originally selected in the protocol was:Death or dependency, defined as a score on the mRS > 2 at outcome assessment in the period day 91 ± 14 days after randomisation. Type: binary.Death at outcome assessment in the period day 91 ± 14 days after randomisation. Type: binary.Score on National Institute of Health Stroke Scale (NIHSS) at outcome assessment in the period day 91 ± 14 days after randomisation. Type: continuous.EuroQoL quality-of-life (EQ-5D-5 L) score at outcome assessment in the period day 91 ± 14 days after randomisation. Type: continuous.World Health Organization Disability Assessment Schedule II (WHODAS 2.0) score at outcome assessment in the period day 91 ± 14 days after randomisation. Type: continuous.Brain infarct size at imaging assessment in the period 48 ± 24 hours after randomisation. Type: continuous.

#### Safety outcomes

Proportion of participants with at least one serious adverse event (SAE) until outcome assessment in the period day 91 ± 14 days after randomisation. Type: binary.Number of SAEs per patient until outcome assessment in the period day 91 ± 14 days after randomisation. Type: rate.

#### Health economic outcome

Incremental cost utility (cost per quality-adjusted life years (QALY)) and incremental cost effectiveness (cost per death or disability averted) ratios. Type: continuous.

### The analysis sets

The analysis populations for the statistical analyses of this trial include the intention-to-treat population, the per protocol set of patients, and the ‘learning curve’ population.

#### The intention-to-treat population of patients

The intention-to-treat (ITT) population is defined as all randomised patients classified according to the intervention to which they were randomised (experimental and control intervention groups) [2].

#### The per protocol set of patients

The per protocol set of patients is the subset of all randomised patients without major protocol violations and classified according to the intervention to which they were randomised. Major protocol deviations encompass: (1) patients in the intervention group who do not reach a body temperature of ≤ 35.0 °C within 3 hours after induction of cooling; or (2) patients randomised in the intervention group who do not achieve at least 6 hours of body temperature at a level of ≤ 35.0 °C during the period from beginning of hour 1 to the end of hour 12 of cooling. According to this definition, the per protocol population will be coded and defined in the data set before data lock, so it cannot undergo changes subsequently.

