#### Sensitivity analyses

The analyses of the primary and secondary outcomes will be repeated using the per protocol population and the ‘learning curve’ population.

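### The per-protocol set excludes only cooled patients, so its tables (like the temperature analyses) reveal the coded arms before the code is due to be broken, and its comparison is open to selection bias in either direction

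*SAP article*

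**What the plan says.** The section on the per-protocol set defines it by the absence of major deviations: "The per protocol set of patients is the subset of all randomised patients without major protocol violations". Two deviations follow. One is "patients in the intervention group who do not reach a body temperature of ≤ 35.0 °C within 3 hours after induction of cooling". The other begins "patients randomised in the intervention group who do not achieve at least 6 hours of body temperature" and concerns time at or below the same threshold during hours 1 to 12 of cooling. No deviation that a control patient could commit is listed. The set is fixed early: "the per protocol population will be coded and defined in the data set before data lock".

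Under Sensitivity analyses, the primary and secondary analyses "will be repeated using the per protocol population" and the learning-curve population. The shells of Tables 3 to 5 show Group 0 and Group 1 in the ITT set and again in the per-protocol set.

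Under Analytical principles the plan adopts a safeguard: "Analyses will be conducted blinded with the two intervention groups coded as, e.g. 0 and 1". Two conclusions are drafted, one for each possible meaning of the codes. "After two abstracts with two conclusions have been written and both accepted by the Steering Group, the code will be broken".

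The outline of the temperature analysis proposes a mixed model with an intervention indicator and a graph of mean temperature in the intervention group. Neither this outline nor the per-protocol text says whether the work comes before or after the code break.

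**The concern.** There are two consequences, and the first is a conflict within the plan itself.

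**Blinding.** If exclusions can occur in one arm only, comparing the per-protocol count with the ITT count by code identifies that arm. An analyst who has seen this can no longer draft two conclusions without knowing which is true. The same holds for anyone on the Steering Group who sees the tables before accepting the abstracts.

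**Selection.** A cooled patient who dies, deteriorates or stops early may not accrue the required hours at temperature and is then removed. A comparable control stays. This sits badly with the plan's own Discussion, which warns that deaths in one group can make that group look better and therefore keeps dead patients in the comparison with the worst score. The per-protocol rule can remove early deaths from the cooled arm alone.

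At stake are a safeguard the plan chose to adopt and the meaning of a sensitivity result that will be printed next to the ITT result without a caution.

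**Working it through.** **Inputs from the SAP.** 800 patients; two-sided alpha 0.05; 63% with mRS > 2 in the control group; 7.25 points as the minimal relevant reduction; stated power 0.55 for that outcome (Table 2).

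**Assumptions.** 400 patients per arm (this document does not state the allocation ratio); the fraction f of the cooled arm excluded; the ratio RR of the excluded patients' risk of mRS > 2 to that of the retained cooled patients. The SAP gives neither f nor RR.

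**Reproducing the plan's figure.** For 63% v 55.75% with 400 per arm, the pooled proportion is 0.59375.
- SE under the null = √(2 × 0.59375 × 0.40625 / 400) = 0.0347.
- SE under the alternative = √((0.63 × 0.37 + 0.5575 × 0.4425) / 400) = 0.0346.
- Power = Φ((0.0725 − 1.96 × 0.0347) / 0.0346) = 0.551, against 0.55 stated.

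Equal arms of 400 are therefore consistent with the plan's own arithmetic.

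**Does the per-protocol table reveal the arm?** As listed, no control can be excluded, so the control row in Table 3 is the same cell by cell in both sets. One excluded cooled patient is enough to separate the codes. With independent failures at rate f, P(at least one exclusion) = 1 − (1 − f)^400. At f = 1% this is 1 − 0.99^400 = 0.982. At f = 5% it is essentially 1.

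**Do the temperature analyses reveal the arm?** A model with an intervention term and a graph of one arm's temperatures show which code was cooled. The notes to Fig. 1 also give different measurement schedules by arm during treatment (every 15 minutes early on in the cooled arm, hourly in controls), so the raw temperature records identify it too.

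**Size of the selection bias with no true effect.** Both full arms have 63% dependent.
- Retained cooled risk r = 0.63 / (f × RR + 1 − f).
- Spurious OR = [r / (1 − r)] / (0.63 / 0.37).
- Rejection is the two-sided rate of a pooled-variance z-test of 400(1 − f) retained cooled patients against 400 controls.

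Example with f = 20% and RR = 1.2: r = 0.63 / 1.04 = 0.606, the difference is −2.4 points, and OR = (0.606 / 0.394) / 1.703 = 0.90.

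| f | RR | r | Difference (points) | OR | Rejection |
|---|---|---|---|---|---|
| 10% | 1.2 | 0.618 | −1.2 | 0.95 | 6.4% |
| 20% | 1.2 | 0.606 | −2.4 | 0.90 | 10.2% |
| 30% | 1.2 | 0.594 | −3.6 | 0.86 | 15.6% |
| 40% | 1.2 | 0.583 | −4.7 | 0.82 | 21.8% |
| 10–40% | 1 | 0.630 | 0 | 1.00 | 5.0% |
| 20% | 1/1.2 | 0.652 | +2.2 | 1.10 | 9.2% |
| 40% | 1/1.2 | 0.675 | +4.5 | 1.22 | 20.9% |

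For scale, the effect the trial was designed around is an OR of 0.74.

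**The case against.** **The list may not be closed.** The verb introducing the two deviations could allow others, and the protocol is not shown. If controls could also be excluded, the arms would be less obvious. But the section goes on to fix the set by this definition, and nothing in it touches controls. The finding holds for the set as listed.

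**Blinding can survive.** ITT is primary for all outcomes, so the abstracts could be written from ITT rows before any per-protocol row exists. That is right: the safeguard fails only if these analyses come first. The plan fixes no order, however, and its shells put both sets in one table.

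**The set is coded before data lock.** This prevents later redefinition. It removes neither the one-sided selection nor the visible difference in counts.

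**The illustration is crude.** It is an unadjusted test of mRS > 2, while the planned analyses adjust for country and seven minimisation factors, and the primary one is ordinal. Adjustment would remove some prognostic selection, though not what arises from events after randomisation.

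**Stronger readings.** A reader might infer that the per-protocol result is the main sensitivity analysis and could rescue a neutral trial. The SAP does not rank it above the learning-curve set or the best/worst-case imputation, and the Multiplicity section rules out a claim of benefit if the primary outcome is neutral. A reader might also infer that the bias must favour cooling. The document gives no exclusion rate and no risk for excluded patients, so neither direction nor size can be established.

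**Conclusion.** The point holds on two counts.

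1. As written, the per-protocol tables and the temperature analyses reveal the cooled arm, and nothing defers them until after the code break. For the per-protocol tables this is near certain: at least 98% if 1% or more of 400 cooled patients fail a criterion. It rests on the listed deviations being complete and on these analyses being seen before the abstracts are accepted.
2. The per-protocol comparison is not a randomised one and may be biased in either direction. Under the assumed exclusions and a 1.2-fold difference in risk, the spurious OR runs from 0.95 to 0.82 one way (10–40% excluded; rejection 6% to 22%) and from 1.10 to 1.22 the other (20–40% excluded). If exclusion is unrelated to prognosis there is no bias. These are illustrations, not estimates for this trial.

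The selection does not touch the ITT primary analysis. The point ranks below a defect in the primary result, but it should be corrected because the remedy is nearly free.

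**What to change.** Add to Analytical principles that both abstracts are written and accepted on the ITT analyses alone. State that the per-protocol flag, the temperature data and everything derived from them (including the per-protocol rows of Tables 3 to 5 and the per-protocol columns of Table 1) are withheld from the blinded analysts and the Steering Group, and produced only after the code is broken. The flag can still be coded before data lock, as planned, by staff outside the blinded analysis.

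Add to Sensitivity analyses, and as a table footnote, that the per-protocol comparison is non-randomised, is subject to selection bias, and has no role in supporting or overriding the ITT conclusion.

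Optionally, supplement it with a complier-average estimate on all randomised patients. This keeps the randomised comparison but gives a wider interval and needs an exclusion restriction. Patients who miss the criteria may still have been partly cooled, so that restriction may fail. It is a possible addition, not a necessary replacement.

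The cost is a few sentences and a later run date for the deferred analyses. No data collection and no clinical criterion changes.
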